### Assessments

Data collection will be based on an assessment protocol for gathering data on sociodemographic, physical, clinical, and biological variables. Patients from the two groups will be evaluated by blind raters at baseline (pre-intervention), after a 4-month intervention period, and 6-month follow-up period. Blood sampling for the analysis of biological parameters will be performed during the same visits. The control group will be evaluated only at baseline.

#### Sociodemographic Variables

Data on sociodemographic variables (age, sex, educational level, socioeconomic level, employment status, family history of psychiatric disorders, number of relapses, years of disease evolution, and number of manic episodes) will be collected at baseline.

#### Physical Parameters

The following physical parameters will be assessed at each of the three visits at the Psychiatric Service of the Alava University Hospital (HUA): body mass (kg) with individuals in light clothing and barefoot using a portable scan body composition and scale (Omron KARADA); height (cm) with participants in a standing position with no shoes using a measuring tape with shoulders in a relaxed position; body mass index will be calculated by dividing body mass to height (kg/m^2^); waist circumference (cm) will be measured using a flexible anthropometric tape midway between the iliac crest and lower rib margin; blood pressure (mm Hg) will be measured in the right arm with the patient in a seated and relaxed position by using a life-support monitor (General Electric carascape U100 Dinamap technology); and a blood sample will be drawn after 12 h overnight fasting to quantify serum levels of triglycerides, glucose and high-density lipoprotein cholesterol. With all this information, the diagnosis of metabolic syndrome will be documented in accordance with the National Cholesterol Education Program Adult Treatment Panel III (ATP III) (34). Thus, patients will have metabolic syndrome if they meet at least two of the following criteria: (1) waist circumference ≥ 102 cm in men or ≥ 88 cm in women; (2) serum triglycerides ≥ 150 mg/dl (8, 3 mmol/L); (3) cholesterol HDL <40 mg/dl (2, 2 mmol/L) in men and <50 mg/dl (2, 8 mmol/L) in women; (4) systolic blood pressure ≥130 mmHg or diastolic blood pressure ≥85 mmHg; (5) serum glucose ≥100 mg/dl (5, 6 mmol/L).

The Ophthalmology Service of the HUA will carry out the study of retinal layers by OCT (HRA+OCT Spectralis, version 6.0, Heidelberg Engineering, Germany): RNFL, GCL and IPL thickness in the two eyes, with each layer divided into segments: overall, temporal, nasal, superior and inferior. In the HUA cardiology service, patients will perform the cardiopulmonary exercise test (CPET) at the baseline visit and after the intervention. At these same visits, in the Nuclear Medicine Service of the HUA, a Dual-energy X-ray absorptiometry (Hologic QDR 4500 W) will be used to evaluate the body composition of participants. This whole-boy scan will be performed to analyze the amount of body fat and muscle mass of participants.

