Previous studies have shown that physical exercise is an effective antidepressant intervention (30), but no studies have been able to provide a comprehensive overview of the mechanisms that produce these benefits in terms of patient prognosis. This fact led us to conduct a longitudinal comparative study to assess the impact on FunctIonality and Neurocognition of an individualized moderate-to-vigorous physical EXercise Training in a population of patients with BD (FINEXT-BD study).

We hypothesize that this intervention will improve the functional status of patients and this improvement will be reflected in physical and biological parameters. Thus, the primary aim of this study will be to investigate whether the implementation of an individualized moderate-to-vigorous physical exercise intensity program as adjuvant therapy to standard drug therapy will improve the functional status of patients with BD, as compared to a group of patients with BD without intervention. The specific secondary objectives of the study will be to: (1) investigate whether the implementation of this exercise program modifies the cognition, the clinical symptoms and incidence of comorbidities; (2) investigate whether the implementation of this exercise program induces changes in the levels of oxidative and inflammatory parameters and these changes correlate with the evolution of clinical symptoms; (3) whether BDNF and TRkB-FL/TRkB-T ratio are associated with the evolution of the patient's functional and neurocognitive capacity, and (4) whether changes in the thickness of retinal layers as measured by OCT correlate with the functionality and neurocognitive function of BD patients.

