### Participants

#### Patients

The sample of patients with BD will be recruited by trained and experienced psychiatrists from patients treated in the Inpatient and Outpatient Unit of Psychiatry of the University Hospital of Alava.

Inclusion criteria will be:

Diagnosis of BD according to the Diagnostic and Statistical Manual of Mental Disorders, Fifth Edition (DSM-5) (31), diagnosis based on semi-structured SCID-P interview (32). The study will involve patients with first-episode or multiple episodes of mania. Patients will be required to be euthymic at baseline, defined as no current diagnosis of an episode of mania, hypomania, or depression. Relapse during follow-up or presence of subsyndromal symptoms at any moment will not be exclusion criteria.Age between 18 and 65 years.Speak Spanish correctly.

Exclusion criteria will be:

Intellectual disability (assessed by DSM-V).History of cranial trauma with loss of consciousness.Physical diseases that cause mental health problems.Pervasive developmental disorders.Pregnancy or breastfeeding.Be classified as “physically active” according to the Global Physical Activity Questionnaire (GPAQ) (33).The presence of a severe or uncontrolled cardiovascular risk factor such as unstable coronary artery disease, uncontrolled hypertension, malignant ventricular arrhythmia, atrial fibrillation, exercise-induced ischemia, and ventricular failure during exercise.Other significant medical conditions including, but not limited to chronic or recurrent respiratory, gastrointestinal, neuromuscular, or any musculoskeletal problems interfering with exercise.The presence of inflammatory diseases.Consumption of anti-inflammatory drugs during the week prior to blood extraction.

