### Exercise Intervention Program

Previous investigations by the exercise specialists who will lead this research have already performed the exercise protocol (69, 70). In short, the experimental group will receive supervised physical exercise treatment by high-intensity interval training (HIIT), alternating high and moderate intensities (20 min). Participants will exercise two non-consecutive days per week for 16 weeks under the supervision of a coach at the facilities provided by the University Hospital of Araba. All the exercises sessions will start and finish with blood pressure monitoring and training intensity will be controlled by HR monitoring (Polar M200, Kempele, Finland) and through the rate of perceived exertion using the Borg's original scale (6–20 point). Each session will include a 10 min warm-up with joint mobility and coordination exercises with continuous leg movement to facilitate the venous return and a 10 min cool-down period with basic core strengthening exercises and passive stretching exercises on the floor to ensure a progressive return to the resting values of both blood pressure and HR. The main portion of the training session will consist of 20 min of aerobic exercises on the bike developing progressively intensity. Intensity will be individually tailored to HR at moderate or vigorous intensities, adjusting the power and speed on the bike, to achieve the planned target HR (Table 1). The exercise specialists will keep detailed records of all the exercise sessions reporting the HR and Borg scale values of every interval. The importance of targeting moderate and high intensity will be emphasized.

**Table 1 T1:** Intervention program for the experimental group by High-intensity physical exercise program on the bike.

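### Metabolic syndrome is scored only from values measured at the visit, so a component controlled by drugs counts as absent and can change a patient's status

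*Protocol article*

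**What the plan says.** In Physical Parameters the article lists weight, height, waist, blood pressure and a fasting blood sample, all taken at each of three visits. It continues: "With all this information, the diagnosis of metabolic syndrome will be documented in accordance with the National Cholesterol Education Program Adult Treatment Panel III". The working rule follows: "patients will have metabolic syndrome if they meet at least two of the following criteria".

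The five criteria are:

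1. Waist: "waist circumference ≥ 102 cm in men or ≥ 88 cm in women".
2. Triglycerides: "serum triglycerides ≥ 150 mg/dl".
3. HDL: "cholesterol HDL <40 mg/dl" in men, with a limit of 50 mg/dl in women.
4. Blood pressure: systolic at least 130 mmHg or diastolic at least 85 mmHg.
5. Glucose: at least 100 mg/dl.

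Three other places bear on this:

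- **Eligibility (Patients).** The cardiovascular exclusion covers severe or uncontrolled risk factors and names "uncontrolled hypertension". It does not name hypertension that is under control. No exclusion is named for treated dyslipidaemia or treated raised glucose.
- **Objectives (Introduction).** Secondary objective 1 asks whether the programme "modifies the cognition, the clinical symptoms and incidence of comorbidities". The Introduction also calls metabolic syndrome a common comorbidity of bipolar disorder.
- **Medication.** The article describes psychiatric treatment as usual (Design), adherence and lithium response (Medication adherence), and recent anti-inflammatory use as an exclusion (Patients; Controls). It does not describe recording antihypertensive, lipid-lowering or glucose-lowering drugs, or using them in the score.

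**The concern.** Criteria 2 to 5 measure the abnormality and its treatment together. A patient whose raised pressure, lipids or glucose has been brought below the cut-off by a drug is scored like a patient who never had the abnormality. Because two components decide the diagnosis, one masked component can be enough to change it.

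Three quantities are at stake: who counts as a case at baseline, who is at risk of becoming a new case, and what a change of status between visits means. An incidence analysis depends on all three. A new prescription can be read as a metabolic improvement, and a patient already under treatment at entry can later be counted as a new case if a reading drifts back above the cut-off.

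**Working it through.** The article gives no prevalence, incidence or sample-size figure for metabolic syndrome, so there is no stated number to reproduce. The check applies the written rule to a patient and then asks how many patients it could affect.

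**Step 1: the rule as written.** Count = number of the five criteria met; syndrome present if count ≥ 2. Take an invented man with waist 104 cm, blood pressure 142/88 mmHg, triglycerides 120 mg/dl, HDL 45 mg/dl and glucose 95 mg/dl.

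| State | Waist | TG | HDL | BP | Glucose | Count | Syndrome |
|---|---|---|---|---|---|---|---|
| Untreated, 142/88 | yes | no | no | yes | no | 2 | yes |
| On a BP drug, 124/78, all else unchanged | yes | no | no | no | no | 1 | no |
| On a BP drug, treated component counted | yes | no | no | yes | no | 2 | yes |

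**Step 2: what this does over time.** The same man produces three different errors, depending on when treatment starts.

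- Treated before baseline: he enters as a non-case and joins the at-risk set. A later reading of 130 mmHg or more, with the waist criterion still met, makes him a new case although the condition preceded the trial.
- Untreated at baseline and treated afterwards: he moves from case to non-case and looks resolved.
- Normal pressure at baseline, raised pressure found and treated between visits: his count stays at 1 and the new case is missed.

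**Step 3: when it matters.** Status changes only if the drug takes the value across the cut-off and the count then falls below two. A treated patient who meets two other criteria is classified the same either way. A treated patient who still reads at or above 130 systolic or 85 diastolic still meets criterion 4.

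**Step 4: possible size.** Both rates here are assumptions, since the article gives neither: 30–50% of patients have the syndrome, and 5–20% of those lose a deciding component through a new drug. Patients reclassified in an arm of 40 = 40 × prevalence × fraction.

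- Low end: 40 × 0.30 × 0.05 = 0.6 patients.
- High end: 40 × 0.50 × 0.20 = 4 patients.

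Each reclassified patient moves an arm's prevalence by 1/40 = 2.5 percentage points, so the range is 0.6 × 2.5 = 1.5 to 4 × 2.5 = 10 points within an arm. This is misclassification within one arm, not a difference between arms. It also leaves out patients already treated at baseline.

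**The case against.** The strongest reply is that the article says the diagnosis follows a cited standard. That source is not at hand, and it may deal with treated patients. A journal article is also condensed, and concomitant-medication recording is often left to the full protocol. This lowers confidence but does not remove the point: the article goes on to print a complete numerical rule, and that rule has no treatment alternative.

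It is also fair to say that objective 1 does not name metabolic syndrome, and that the Statistical Analysis section gives it no specific analysis. The link runs through the Introduction, which calls it a common comorbidity, and through its reassessment at every visit. Further, the objective concerns incidence. A baseline case who appears to resolve is not an incident case, so the errors that bear most directly on the objective are the wrong at-risk set and the missed new case.

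A reader might go further and infer that the exercise arm will show a false metabolic benefit, because "All the exercises sessions will start and finish with blood pressure monitoring". Two sessions a week for 16 weeks with two readings each gives 2 × 16 × 2 = 64 scheduled readings that the other arm does not have. The documents do not support that inference:

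- Nothing says that session readings reach a prescriber or lead to treatment.
- Both arms receive usual care with monthly visits (Design). Both have pressure measured at the three study visits and during the exercise test.
- Uncontrolled hypertension is excluded at entry, which limits what is left to discover.
- The mechanism could touch only one of the five components. It says nothing about lipid-lowering or glucose-lowering drugs.
- The number of readings is not a number of drug starts. Any figure for a difference between arms would need an assumed count in one arm and an assumed count in the other.

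The treating psychiatrist knows of the patient's participation (Randomization and Blinding), so unequal drug starts are possible, but they are not shown.

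**Conclusion.** The point holds as a badly fixed outcome definition. Applied as written, the rule misclassifies any patient whose drug-controlled component would have brought the count to two. It can also turn a prescription started between visits into a hidden new case or an apparent resolution. This affects baseline status, the at-risk set and change over the three visits.

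It does not follow that every treated patient is misclassified, or that the exercise arm is favoured. The size is unknown; the 0.6 to 4 patients per arm of 40 rests entirely on the two assumed rates. The outcome is secondary, and the primary outcome (functioning) and the sample size are not affected. The change is worth making because it is cheap and because treatment status at a past visit may be hard to reconstruct later.

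**What to change.** In Physical Parameters, score each of criteria 2 to 5 as met if the measured value reaches the cut-off or the patient is currently receiving drug treatment for that abnormality. Apply this identically in both arms at all three visits. Record antihypertensive, lipid-lowering and glucose-lowering drugs at each visit, with the reason for use.

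Add a sensitivity analysis that scores the syndrome from measured values only and flags patients who started or changed such treatment after baseline. Report both scorings, with the number of drug starts by arm.

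The cost is one clause in the definition and a short medication record at three visits. There are two downsides. A patient on treatment cannot show resolution of that component, however far the value falls. And if drug starts do differ between arms, the new rule can itself add detection bias, because a newly treated patient counts as positive even when the visit values were below the cut-off. That is why neither scoring should be reported alone. The change concerns outcome scoring only and leaves clinical care as it is.

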## Introduction

Bipolar disorder (BD) is a mood disorder affecting about 400 million people worldwide (1). This psychiatric disease is a chronic disorder associated with cognitive dysfunction, increased mortality and intensive use of healthcare services (2, 3). The management of BD involves a combination of pharmacological therapies and psychosocial interventions including, but not limited to, cognitive-behavioral therapy, functional remediation, family psychoeducation, social skills training and protected employment (4). Despite therapies, the risk of recurrence is high, and patients often do not recover completely. Failure of current therapies to induce the remission of BD symptoms has led researchers to focus their efforts on developing more effective treatments (5).

In the search for new therapeutic strategies, physical exercise has been found to play a relevant role in the treatment of psychiatric disorders (6). Thus, physical exercise is not only effective in improving cardiorespiratory function, physical status, and metabolic syndrome (common comorbidities in BD), but it has also proven to reduce depressive symptoms and suicidal ideation (7).

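### The mmol/L limits for triglycerides and HDL in the metabolic-syndrome definition were converted with the glucose factor and contradict the mg/dl limits beside them

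*Protocol article*

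**What the plan says.** The Physical Parameters section of the protocol article derives a yes/no diagnosis of metabolic syndrome from measurements taken at each of the three visits. Three of the five criteria are laboratory values, each given first in mg/dl and then in mmol/L in parentheses (the decimal comma is printed with a space):

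- triglycerides and HDL in men: "serum triglycerides ≥ 150 mg/dl (8, 3 mmol/L); (3) cholesterol HDL <40 mg/dl (2, 2 mmol/L) in men"
- HDL in women: "<50 mg/dl (2, 8 mmol/L) in women"
- glucose: "serum glucose ≥100 mg/dl (5, 6 mmol/L"

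The section does not say which unit governs, or in which unit the laboratory reports.

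The diagnosis bears on secondary objective 1, which asks whether the exercise program "modifies the cognition, the clinical symptoms and incidence of comorbidities". That objective does not name metabolic syndrome, but the Introduction lists "metabolic syndrome (common comorbidities in BD") among the conditions that exercise improves.

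**The concern.** Converting mg/dl to mmol/L depends on the molar mass of the substance. Triglycerides, cholesterol and glucose are different molecules, so one divisor cannot serve all three. Yet the printed pairs all imply nearly the same divisor. If it is the glucose divisor, the lipid limits in parentheses are not equivalents of the mg/dl limits. The definition then contains two different rules for the same diagnosis.

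What is at stake is the classification of patients on a secondary comorbidity outcome. The two lipid errors act in opposite directions. The mmol/L triglyceride limit is too high, so fewer patients reach it. The mmol/L HDL limits are too high for a criterion met by falling below them, so more patients meet it.

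**Working it through.** **Inputs from the protocol article (Physical Parameters):** triglycerides 150 mg/dl and 8.3 mmol/L; HDL in men 40 and 2.2; HDL in women 50 and 2.8; glucose 100 and 5.6.

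**Inputs assumed (physical constants, not in the article):** molar mass of glucose 180.16 g/mol, of cholesterol 386.65 g/mol, and of triglycerides about 885 g/mol. Serum triglyceride is a mixture, so a range of 800 to 900 is carried.

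**Formula:** mmol/L = mg/dl × 10 / molar mass. The divisor is therefore molar mass / 10: 18.016 for glucose, 38.665 for cholesterol and about 88.5 for triglycerides.

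**Step 1. Divisor implied by each printed pair**, with the range that rounding to one decimal allows:

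| Pair | Implied divisor | Range |
|---|---|---|
| Triglycerides 150 / 8.3 | 18.07 | 17.96 to 18.18 |
| HDL men 40 / 2.2 | 18.18 | 17.78 to 18.60 |
| HDL women 50 / 2.8 | 17.86 | 17.54 to 18.18 |
| Glucose 100 / 5.6 | 17.86 | 17.70 to 18.02 |

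A single divisor between 17.96 and 18.02 fits all four pairs, and the glucose divisor of 18.016 lies in that interval.

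**Step 2. Reproduce the printed figures with the glucose divisor.** 150/18.016 = 8.33; 40/18.016 = 2.22; 50/18.016 = 2.78; 100/18.016 = 5.55. These round to the printed 8.3, 2.2, 2.8 and 5.6 (the last from 5.551).

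**Step 3. Convert each limit with its own molar mass.**

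- Triglycerides: 1500/885 = 1.69 mmol/L (1.67 at 900, 1.88 at 800).
- HDL men: 400/386.65 = 1.03 mmol/L.
- HDL women: 500/386.65 = 1.29 mmol/L.
- Glucose: 1000/180.16 = 5.55 mmol/L, so the printed 5.6 is right.

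**Step 4. Read the printed mmol/L limits back into mg/dl.**

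- Triglycerides: 8.3 × 88.5 = 735 mg/dl (664 to 747 over the range), which is 4.9 times 150.
- HDL men: 2.2 × 38.665 = 85 mg/dl, 2.1 times 40.
- HDL women: 2.8 × 38.665 = 108 mg/dl, 2.2 times 50.

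**Step 5. Effect on individual men.**

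| Triglycerides, HDL (mg/dl) | Met with the mg/dl limits | Met with the printed mmol/L limits |
|---|---|---|
| 300, 38 | both | HDL only |
| 160, 45 | triglycerides only | HDL only |
| 110, 60 | neither | HDL only |

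The count of criteria met can fall, stay the same or rise.

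**Step 6. Conditional illustration of prevalence.** This uses the article's own counting rule ("patients will have metabolic syndrome if they meet at least two of the following criteria") and assumptions that are not trial data: the five criteria are independent and equally common under the mg/dl limits; under the printed mmol/L limits, HDL is met by 99% and triglycerides by 1%.

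At 30% per criterion with mg/dl limits: 1 − 0.7⁵ − 5 × 0.3 × 0.7⁴ = 1 − 0.168 − 0.360 = 47%.

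With mmol/L limits:

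- P(none met) = 0.7³ × 0.01 × 0.99 = 0.003.
- P(exactly one met) = 3 × 0.3 × 0.7² × 0.01 × 0.99 + 0.7³ × (0.99² + 0.01²) = 0.004 + 0.336 = 0.341.
- Prevalence = 1 − 0.003 − 0.341 = 66%.

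The same sums give 26% against 49% at 20% per criterion, and 66% against 78% at 40%. Independence widens the gap. With a common latent normal correlation of 0.3 between criteria, the 30% case becomes 44% against 58%; with 0.5 it becomes 41% against 53%.

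**The case against.** The error sits only in parentheses. Each laboratory limit is stated first in mg/dl, and none of those is disputed. Harm needs a further step: results held in mmol/L and compared with the parenthetical figures. Nothing in the article says that the laboratory reports or the analyst codes in mmol/L. This stands, and it makes the consequence conditional. It does not remove the contradiction, because no text says that mg/dl governs.

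The outcome is also peripheral: one comorbidity within one of four secondary objectives, and linked to that objective by inference. Any miscoding would apply the same rule to both randomised groups, so there is no evident reason for it to favour one of them. This stands too.

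A reader might infer more: that the decision threshold itself is wrong, that the trial's metabolic-syndrome prevalence will be inflated, or that real change after exercise will be hidden. The article does not support these. The mg/dl limits are intact. The patient with triglycerides of 300 and HDL of 38 mg/dl loses a criterion, so the shift is not always upward. The article gives no lipid distribution from which a prevalence or a loss of sensitivity could be calculated. The 99% and 1% rates in the illustration are assumptions.

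**Conclusion.** The point holds as a minor correction. Three of the four printed mmol/L limits are wrong, because they were evidently obtained with the glucose divisor. The triglyceride figure is too high by a factor of about 4.9 and the two HDL figures by about 2.1 and 2.2. This rests on molar masses as physical constants. The only uncertain one, for triglycerides, does not alter the conclusion anywhere between 800 and 900 g/mol.

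The effect on data depends on the unit in use. With mg/dl alone, classification is as intended. With mmol/L against the printed limits, classification can change in either direction. Under the stated assumptions the net shift in prevalence would be upward: about 19 points with independence and 30% per criterion (65.6% less 47.2% is 18.4 before rounding), and 12 to 14 points with correlated criteria. These figures show that the choice of unit could matter; they do not predict this trial's results. The primary functional outcome and the sample-size calculation are not touched.

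**What to change.** In Physical Parameters, replace the lipid parentheses with the arithmetic equivalents of the stated mg/dl limits: triglycerides about 1.7 mmol/L, HDL about 1.0 mmol/L in men and 1.3 mmol/L in women. Leave the glucose pair as it is. Alternatively, delete the mmol/L figures and state that mg/dl governs.

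Then confirm the unit in which the laboratory reports each analyte, and check that the derivation code compares values with limits in that same unit. If any classification has already been derived, rerun it after this check.

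The cost is one line of text and one check of the code. Visits, measurements, sample size and the primary analysis do not change.
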